#### 2.3.3. Analysis and Findings

The interviewers, along with three other physiotherapists, two specializing in Pelvic and Women’s Health (PT4 and PT5) and one expert in qualitative research (PT6), will transcribe the recorded interviews. The data will be coded to maintain the participants’ anonymity, based on whether the interview is individual or group-based, and according to the order of participation. The researchers who perform the transcriptions will reach a consensus on the identified themes and group them into categories. For transcription, coding, and categorization of the information extracted from the interviews, the software ATLAS.ti 25 (Scientific Software Development GMBH, Berlin, Germany) will be used.

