#### 2.3.1. Research Teams and Reflexibility

The individual interviews and focus groups will be conducted by two physiotherapists specialized in Pelvic and Women’s Health, who are women, mothers, university professors, and hold a PhD. Interviewer 1 (PT1) will be familiar with the participants in advance, as she is the blinded evaluator of the RCT. This evaluator will interview the women who have already completed the follow-up in order to avoid conflicts related to the potential disclosure of the intervention group during the interviews. Interviewer 2 (PT2) will not know the participants in advance and will conduct interviews with women who are between the A2 and A4 follow-up assessments. Both evaluators have prior experience conducting individual interviews and focus groups within the framework of qualitative studies in women’s health.

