#### 2.3.2. Qualitative Study Design

The theoretical framework and methodological orientation for the qualitative part of the RASDOP study is based on phenomenology. The main objective will be to understand the experience of postpartum women in adhering to a physiotherapy treatment aimed at improving their postpartum pelvic pain.

Women who have completed the 12 individual physiotherapy sessions will be included, regardless of the assigned treatment group of the RCT. Women will be divided into two groups: one consisting of women who are in the follow-up period (3 to 12 months after completing the intervention), or those who have already finished their participation in the study (> 12 months after the physiotherapy intervention). The recruitment will be consecutive, and the study will end when data saturation is reached. Data saturation will be deemed achieved when the information gathered aligns with that from earlier interviews.

All interviews will be conducted face-to-face and will take place in a classroom in the Nursing and Physiotherapy Building at the University of Alcalá, near the FPSM Research Group laboratory. The focus groups will consist of four to six women who do not know each other beforehand. In the interviews, only the participating postpartum women and one of the interviewers (PT1 or PT2) will be present. The interviewers will use a pre-designed question guide (Table 3), and the sessions will be audio-recorded with the prior consent of the participants.

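### Section 2.3.3 does not keep the blinded assessor (PT1) away from interviews of women still in follow-up, which undercuts the safeguard in Section 2.3.1

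*Protocol article*

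**What the plan says.** Section 2.3.1 (Research Teams and Reflexibility) gives the assessor a second role: "Interviewer 1 (PT1) will be familiar with the participants in advance, as she is the blinded evaluator of the RCT". It limits whom she may interview to women who have completed follow-up, and gives the reason: "in order to avoid conflicts related to the potential disclosure of the intervention group during the interviews". The other interviewer, PT2, "will conduct interviews with women who are between the A2 and A4 follow-up assessments".

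Section 2.3.3 (Analysis and Findings) describes what happens to the recordings. "The interviewers, along with three other physiotherapists" (PT4, PT5 and PT6) "will transcribe the recorded interviews". It continues: "The researchers who perform the transcriptions will reach a consensus on the identified themes and group them into categories". The data are coded by interview type and order of participation.

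Section 2.2.4 (Follow-Up) has PT1 carry out every assessment from A0 to A4. Section 2.1 makes the outcome assessors the only masked party; participants and treating physiotherapists are not masked.

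**The concern.** The restriction in Section 2.3.1 rests on a sound premise: a woman talking about her treatment may reveal her arm, and PT1 should not hear this while she still has to examine that woman. The restriction covers only the interview itself. The same content reaches whoever listens to the recording, reads the transcript or sits in the theming discussion, and Section 2.3.3 places PT1 in that group without a limit on whose interviews or when.

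What is at stake is the masking of some A3 and A4 examinations. Trigger-point palpation in particular relies on the examiner's judgement, and Section 3.1 states an expectation that the radiofrequency group will do better on all variables, naming a lower presence of trigger points among them. An examiner who knows the arm and shares that expectation is the situation that assessor masking is meant to prevent.

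**Working it through.** No figure of the plan is in question, so the check traces PT1's role through the text.

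1. **Who assesses.** PT1 performs all assessments (Section 2.2.4). By the time a woman is interviewed between A2 and A4, PT1 will have seen her at A0, A1 and A2, and still has A4, or both A3 and A4, to perform.
2. **What the safeguard covers.** Section 2.3.1 limits whom PT1 interviews. Section 2.3.2 adds that only the women and one interviewer are present, so PT1 is not in the room for PT2's sessions. Up to this point masking is protected.
3. **Who handles the recordings.** Section 2.3.3 uses the plural for the interviewers. Section 2.3.1 names exactly two, PT1 and PT2. The transcribing team is therefore PT1, PT2, PT4, PT5 and PT6, and the same people agree the themes. Neither sentence excepts women still in follow-up.
4. **When.** No date is given for transcription or theming. Section 2.3.2 recruits consecutively and stops at saturation, judged by whether new information matches that from earlier interviews. This implies some analysis while interviewing continues, when some interviewed women may not have reached A4.
5. **Whether the arm could be recognised.** The interview guide (Table 3) does not ask about the arm, but question 1 asks about experience of the programme and question 7 about treatments thought unnecessary. In the radiofrequency group the device is used from the third of 12 sessions (Section 2.2.5), so in up to 12 − 2 = 10 sessions. It could readily be mentioned.
6. **Whether the woman could be recognised.** The code based on interview type and order removes the name. It does not remove the voice from an audio recording or the treatment content from a transcript, and PT1 knows the women.
7. **Which outcomes are exposed.** PT1 measures trigger points, muscle tone and strength by dynamometry, and levator hiatus length by ultrasound. The FSFI, PFDI-20, PFIQ-7 and Broome scale are completed online by the participant (end of Section 2.2.3). The pain VAS is not in that online list, and Table 1 places pain intensity within the physiotherapy assessment, but the participant marks the line herself. A0 to A2 precede these interviews and are unaffected.

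Steps 2 and 3 are the inconsistency: disclosure to PT1 is prevented in the interview room and left open at transcription and theming.

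**The case against.** The strongest reply is that Section 2.3.3 describes a team effort and does not say that PT1 handles PT2's recordings. Each interviewer might transcribe her own sessions, or the work might wait until follow-up ends. The authors saw the risk, and a condensed article may leave the allocation of files to the full protocol. This stands in part: a reader might infer that blinding will be lost, and the document does not say so. It is a risk left open. The reply does not remove the point, because the article does state who transcribes and who agrees the themes, and that statement conflicts with its own safeguard. Even if each interviewer transcribed only her own sessions, the theming consensus would still include PT1.

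A second reply is that the data are coded. That helps with written transcripts but not with audio heard by someone who knows the speakers.

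Three stronger readings are tempting and not supported:

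- *Mixed-arm focus groups unblind the assessor.* Women are eligible "regardless of the assigned treatment group of the RCT", so groups may mix arms. But participants already know their own arm, PT1 is not present at PT2's sessions, and the article does not say which format is used during follow-up. Any effect on later self-report is conjecture.
- *PT4 transcribing accounts of treatment she delivered breaks masking.* PT4 does not assess outcomes. This is a question of reflexivity in the qualitative work.
- *A given percentage of the sample is assessed unblinded.* The number of interviews is not stated. Any percentage would have to assume that number, that each woman reveals her arm, and that PT1 processes each recording before that woman's A4.

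**Conclusion.** The point holds as an inconsistency between Sections 2.3.1 and 2.3.3. Followed as written, Section 2.3.3 permits PT1 to hear or discuss interviews of women she has yet to examine, so her masking may be broken before A3 or A4.

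Its size is limited. It concerns only women interviewed between A2 and A4, a subsample recruited to saturation and of unstated number. For each, two assessments at most are exposed, and only one if the interview follows A3. It bears mainly on PT1-measured secondary outcomes. Both primary outcomes are reported by women who know their arm, so they depend much less on PT1's masking. The conclusion assumes that PT1 takes part in transcription or theming before the woman's A4 and that the arm can be recognised from what is said; the text allows the first and makes the second plausible.

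It does not threaten the main comparison, but it deserves correction because assessor masking is the only masking the trial claims, and masking once broken cannot be restored.

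**What to change.** Reconcile the two sections with one added statement in Section 2.3.3: PT1 has no access to recordings, transcripts or theming meetings concerning any woman who has not completed A4. PT2, PT5 and PT6 handle that material, and PT1 joins that part of the analysis only once A4 is done. The statement should be in force before any interview held during follow-up is transcribed.

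No new staff are needed, since all three are already on the transcribing team and none has an assessment role in the trial. The cost is that part of the qualitative analysis finishes later. The interview schedule, the focus groups and the rest of the qualitative design can stay as they are.

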## 3. Results

The RASDOP study aims to assess the effectiveness and safety of including non-ablative radiofrequency as part of a multimodal physiotherapy treatment for postpartum pelvic pain. Additionally, the study seeks to understand the experiences of these women regarding adherence to conservative treatment and home-based advice.

### 3.1. RASDOP Randomized Controlled Clinical Trial Expected Results

The multimodal physiotherapy intervention, based on therapeutic education, PFMT, treatment of MPS in the abdominal and/or PFM, and the use of radiofrequency in women with pelvic pain after childbirth, is expected to significantly improve pelvic floor symptoms in these women. Thus, the RASDOP study is proposed as a solution to improve symptoms related to pelvic pain, the potential occurrence of urinary incontinence, increased urinary frequency, or even the presence of involuntary gas leakage in the postpartum period.

A significant improvement is expected in sexual function, particularly in the domains of lubrication, orgasm, and pain, as assessed by the FSFI questionnaire. Regarding distress and the impact of other pelvic floor dysfunctions, such as lower urinary tract issues, pelvic organ prolapse, and anorectal dysfunctions, evaluated through the PFDI-20 and PFIQ-7 questionnaires, a decrease of more than a 23% in the scores is anticipated, indicating an improvement in symptoms and a reduced impact on quality of life [48].

An increase in the strength of the PFM is expected, as measured by vaginal dynamometry, due to the performance of PFMT and the adoption of healthy PFM protection habits. In contrast, an improvement in the relaxation capacity and elasticity of the PFM is anticipated, as assessed by transperineal ultrasound.

It is expected that the presence of MTrPs in the abdominal muscles and PFM will decrease or even be eliminated. In cases where MTrPs are still palpated, it is anticipated that they will be latent and not trigger painful symptoms in the women.

The Broome scale will be used to assess self-confidence and self-efficacy in performing PFMT, as well as changes in lifestyle behavior, which are expected to help sustain treatment benefits in the long term. It is anticipated that participants in both groups will achieve a score of over 66 points on the Broome scale during the post-treatment and follow-up evaluations, indicating a high perception of self-efficacy [46].

Although both intervention groups are expected to show significant improvements between the pre- and post-treatment assessments, and maintain their results at 3-, 6- and 12-month stages post-treatment, it is anticipated that these improvements will be greater in all variables in the RMP-G group, particularly in sexual function, pain reduction, and the lower presence of MTrPs.

No adverse effects are expected in either intervention group. The authors believe that interventions will not need to be postponed, nor will participants require analgesic medication.

### 3.2. RASDOP Qualitative Study Expected Results

The postpartum period is a vulnerable time during which women must balance their physical and mental recovery from pregnancy and childbirth with their new role and responsibilities as mothers. This qualitative study aims to delve into the experiences of postpartum women, exploring the facilitators and barriers they encounter in undertaking a conservative treatment to address their postpartum pain symptoms and adhering to healthcare recommendations. This will enable clinicians to propose interventions that are not only effective and safe but also tailored to the unique challenges faced by women during the postpartum period.

## 4. Discussion

To the authors’ knowledge, this is the first RCT with evaluator blinding to compare the effectiveness of a multimodal physiotherapy treatment versus a multimodal treatment that includes non-ablative radiofrequency in managing pelvic pain and sexual function from six weeks to six months postpartum. The significance of the RASDOP study lies in addressing the fact that nearly 50% of women develop symptoms of pelvic pain and/or dyspareunia following childbirth [12,13]. If left untreated, this pain can persist over time [49], negatively impacting sexual function, mental health [50], quality of life, and even the desire to have more children.

Previous studies have evaluated the efficacy of radiofrequency in pelvic pain immediately after childbirth [51,52]. These include two double-blind RCTs comparing the immediate use of radiofrequency versus placebo in women following vaginal delivery. Two consecutive sessions were conducted during the participants’ hospital stay, and perineal pain was assessed at rest, while sitting, and during walking. Bretelle et al. [51] reported improvements in walking pain and reduced analgesic consumption in the study group. In contrast, Sierenska et al. [52] found that radiofrequency improved pain and discomfort at rest, while sitting, and while walking but did not observe a reduction in the consumption of paracetamol or ibuprofen. In the acute phase, perineal trauma can be the primary source of pain, which may sometimes improve with medication or local cooling [53]. However, this pain can persist over time, potentially involving other structures, such as the PFM, as the primary source of discomfort. The RASDOP study proposes applying radiofrequency not only to scars but also to the PFM and abdominal muscles, aiming to improve the MTrPs in these muscles. Radiofrequency has only demonstrated short-term effects, and existing studies have heterogeneous protocols, small sample sizes, or lack a control group [28]. Therefore, more evidence is needed to support the use of radiofrequency for pelvic pain, as well as the additional financial cost associated with this technology. Additionally, radiofrequency is a passive treatment technique, while maintaining long-term benefits requires behavioral modifications and the adoption of active treatment strategies [54]. Therefore, the RASDOP study will include educational management and PFMT in both treatment groups.

Descriptive studies in women experiencing pelvic pain during the postpartum period report alterations in the PFM, including decreased strength and neuromuscular activation [44], reduced tone [44,55], increased tenderness, delayed voluntary activation of the PFM, and abdominal changes such as increased interrectus distance and greater distortion of the linea alba [55]. MPS is a highly prevalent clinical condition in musculoskeletal disorders and has also been shown to be present in various persistent pelvic pain syndromes, such as in women with endometriosis [56] or primary dysmenorrhea [57]. Moreover, the presence of MPS in the PFM has been diagnosed in up to 85% of women with pelvic floor dysfunctions. It has been associated with an increased sensation of pelvic pressure and heaviness in women with pelvic organ prolapse, as well as pain in the lower abdomen and difficulty emptying the bladder in women with urinary symptoms. [19]. Similarly, tenderness in the PFM is associated with dyspareunia and sexual dysfunction, with MPS acting as a perpetuating factor for pain during sexual intercourse [58]. Li et al. [29] also focused on treating MPS in the PFM during the postpartum period, comparing the use of radiofrequency with manual treatment of MTrPs. Both groups achieved pain reduction with no statistically significant differences between them. However, the group treated with radiofrequency experienced an increase in vaginal laxity and improved perceived comfort. Nonetheless, neither group showed improvements in the contractile capacity or neuromuscular activity of the PFM. This may have been due to the absence of specific PFMT in the intervention protocol. The RASDOP study proposes a multimodal physiotherapy treatment that includes PFMT alongside an educational strategy. The aim is to enhance PFM properties as both a protective and therapeutic factor for MPS, which will also contribute to improving sexual function [59]. This approach aligns with international recommendations for preventing pelvic floor dysfunctions during the postpartum period [30].

The classification of pelvic pain is controversial and varies depending on the source consulted. This study will include women with pelvic pain without infection or obvious local pathology, which, according to the International Association for the Study of Pain (IASP) classification, is considered primary pelvic pain syndrome [1]. Since the study will assess the presence of MPS in PFM and abdominal muscles, we will follow the classification provided by the European Association of Urology [2], based on IASP recommendations. Therefore, primary pelvic floor muscle pain syndrome and coccyx pain syndrome, both associated with musculoskeletal pain, will be included.

Among the strengths of the RASDOP study is its design as an RCT conducted by experienced physiotherapists specializing in clinical practice and research in Pelvic and Women’s Health. Participants will be referred by a gynecology service that has maintained a referral relationship for over 15 years, ensuring high-quality conservative treatment for women—a service currently not provided free of charge in Spain. The study’s rigorous design will allow for the evaluation of the efficacy and safety of incorporating radiofrequency technology, an increasingly utilized intervention in clinical settings but with limited supporting evidence to date. Another notable strength is the comprehensive outcome measures to be collected. These will include subjective aspects and quality-of-life impacts, as well as objective local physical changes in the pelvic floor. This will be the first study to assess changes in sexual function and other pelvic floor dysfunctions, such as urinary and/or anal incontinence and pelvic organ prolapse, as well as changes in PFM tone, strength, and morphology in postpartum women experiencing pain who undergo physiotherapy treatment that incorporates radiofrequency. Additionally, the follow-up period will span one year, whereas published studies in this field have only reported immediate post-intervention results [29,51,52].

As a limitation, considering the multifactorial etiology of postpartum pain, hormonal factors may predispose women to greater sexual dysfunction, such as genitourinary syndrome of lactation [60]. To address this, variables related to changes in breastfeeding and the return of menstruation will be collected, as these factors may influence the presence or absence of pelvic pain and sexual function. Additionally, the personal process of role transitions that women experience during this stage of life may play a significant role in sexual dysfunction, beyond purely physical factors [61]. Therefore, another limitation of this study is the absence of a prior neuropsychiatric evaluation. To mitigate this, participants will be asked whether they have previously attended or are currently attending a mental health service. For immediate postpartum perineal pain, the standard medication protocol consists of paracetamol or non-steroidal anti-inflammatory drugs as needed [62,63]. Since medication use will not be altered within the study, any intake by participants will be recorded at each assessment.

If the multimodal physiotherapy treatment that includes radiofrequency is proven to be effective and safe in managing postpartum pelvic pain and sexual function, this conservative therapeutic strategy could be widely implemented to support these women. Furthermore, the qualitative study will provide insights into the factors influencing adherence to healthy habits and home exercises among women experiencing postpartum pain. This knowledge will facilitate the development of treatment programs designed to ensure long-term effectiveness by promoting patient adherence and motivation.

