#### 2.2.1. Study Participants

Postpartum women experiencing pelvic pain following a vaginal delivery, referred by the Gynecology and Obstetrics Department of Príncipe de Asturias University Hospital for physiotherapy assessment. Physiotherapy assessments and treatments will be conducted at the laboratory of the Physiotherapy in Women’s Health (FPSM) Research Group at the University of Alcalá.

The inclusion criteria will be primiparous women who have had a vaginal delivery, within the past 6 weeks–6 months, experiencing postpartum pelvic pain with an intensity of ≥4 cm on the visual analog scale, and who have read, understood, and freely signed the informed consent. Women will be excluded if they are multiparous, have undergone instrumental vaginal delivery or cesarean section, experienced avulsion of the levator ani muscle, sustained a third- or fourth-degree perineal tear, have a history of pelvic fractures and/or neoplasms, are pregnant, have neurological conditions, an active vaginal or urinary tract infection, an intrauterine device with metallic components, or cognitive, auditory, and/or visual impairments that prevent them from understanding the information, responding to questionnaires, providing consent, and/or participating in the study. Women who have received or are currently undergoing medical or physiotherapeutic treatment for pelvic pain will also be excluded. The enrollment, allocation, treatment, and follow-up scheme for the participants is shown in Figure 1.

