#### 2.2.2. Sample Size

The sample size was calculated based on the results obtained by Citak et al. [35], using the Female Sexual Function Index (FSFI) scores as a reference and the statistical program GRANMO 8.0 (Datarus, Barcelona, Spain). Assuming a two-tailed test with an alpha risk of 0.05 and a statistical power greater than 0.8, 62 participants per group will be required to detect a difference of 2.4 points or greater. A common standard deviation of 4.5 was assumed. Additionally, a 10% dropout rate was accounted for in the estimation.

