#### 2.2.5. Intervention

Participants will be randomly assigned in a 1:1 ratio to one of two intervention groups using a computer-generated randomization sequence (Epidat 4.2, Xunta de Galicia, Spain). To ensure allocation concealment, the randomization sequence will be generated in advance by an independent researcher and stored in sealed, opaque, consecutively numbered envelopes. These envelopes will be securely kept and opened only by the designated physiotherapist (PT2) at the time of each participant’s enrollment. PT2 will not be involved in participant assessment or treatment to prevent potential allocation bias. Block randomization with variable block sizes will be used to maintain balance between groups throughout the study.

Participants will be allocated to either the active control group receiving multimodal physiotherapy (MP-G) or the experimental group receiving multimodal physiotherapy including radiofrequency (RMP-G). Both interventions will be individualized and administered by physiotherapists specializing in Pelvic and Women’s Health (PT3 and PT4), who will remain blinded to group allocation to ensure assessor masking. The approximate session duration will be 45 min per session, twice a week for 6 weeks, totaling 12 sessions. Both groups will receive therapeutic education, specific PFMT, and conservative and/or invasive treatment for MPS, with the addition of radiofrequency in the RMP-G. The details of each treatment strategy are explained below.

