#### 2.2.6. Statistical Data Analyses

A descriptive analysis of each collected variable will be conducted. For continuous variables, means, medians, standard deviations, and quartiles will be calculated, depending on whether the assumption of normality is met, as determined beforehand using the Shapiro–Wilk test. Qualitative variables will be described with absolute and relative frequencies in percentages.

For intragroup comparisons over time (A0–A4), if continuous variables follow a normal distribution, repeated-measures ANOVA will be used. If the data do not follow a normal distribution, the Friedman test will be used. For ordinal variables (FSFI, PFDI-20, PFIQ-7, Broome Scale), the Friedman test will be used for comparisons across more than two time points, or the Wilcoxon signed-rank test for comparisons between two time points, regardless of whether they follow a normal distribution. For dichotomous variables, the McNemar test will be applied for two time points, and the Cochran Q test will be used for multiple time points.

To determine the association between groups at each time point, a dichotomous independent variable and a quantitative dependent variable with a parametric distribution, the independent Student’s t-test will be used if the data follow a parametric distribution. If the assumption of normality is violated, the Mann–Whitney U test will be applied. For ordinal variables, the Mann–Whitney U test will be used to compare two independent groups, and the Kruskal–Wallis test will be applied for comparisons across more than two groups. For dichotomous variables, the Chi-square test will be used, and Fisher’s exact test will be applied if the expected frequency is less than 5. The effect will be assessed by the difference in means, and the precision will be measured using the 95% confidence interval.

The main analysis to compare the groups will be adjusted to the baseline pre-intervention values of the outcome variables. In all cases, a significant level of *p* < 0.05 will be used. The statistical software SPSS, version 29, IBM, will be employed.

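### Breastfeeding and menstruation data are collected to address a possible influence on both primary outcomes, but the stated main analysis gives them no role

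*Protocol article*

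**What the plan says.** Section 4 (Discussion) of the protocol article names hormonal influences during lactation as a limitation, because they may predispose women to sexual dysfunction. Its remedy is data collection: "variables related to changes in breastfeeding and the return of menstruation will be collected, as these factors may influence the presence or absence". The sentence ends by naming pain and sexual function. Section 2.2.3 lists pelvic pain (VAS) and sexual function (FSFI) as the primary outcomes, so the remedy concerns exactly these two.

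Table 1 places breastfeeding and menstruation in the gynecological history, taken at A0 and updated at A1–A4 only if something changes.

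Section 2.2.6 says of the main comparison: "The main analysis to compare the groups will be adjusted to the baseline pre-intervention values of the outcome variables". It names no other covariate. The tests it lists for group comparisons at each time point are Student's t-test and Mann–Whitney for quantitative variables, and Mann–Whitney for ordinal ones, among which it counts the FSFI.

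Section 2.2.1 admits women who delivered "within the past 6 weeks–6 months". Section 2.2.5 uses 1:1 randomisation in variable-size blocks and names no stratification factor.

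**The concern.** The article presents a limitation as addressed, but the step it takes is only to record the variables. Nothing in section 2.2.6 uses them, so the two sections do not connect.

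Two things are at stake. The first is precision: breastfeeding status at A0 is already recorded, and weeks since delivery must be known to check eligibility, so information that may explain outcome variation is available and unused. The second is clarity. The Discussion speaks of changes in breastfeeding and the return of menstruation, most of which will occur after randomisation. With no stated use, the wording leaves room for someone later to adjust for them in the main model, where they do not belong. Status at A0 and later change need to be kept apart, and the article does not do so.

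**Working it through.** **Inputs from the article.** Section 2.2.2 gives a two-sided alpha of 0.05, power above 0.8, an SD of 4.5 and an allowance of 10% for dropout. Its result is "62 participants per group will be required to detect a difference of 2.4 points or greater". Section 2.2.5 gives the allocation ratio: "Participants will be randomly assigned in a 1:1 ratio to one of two intervention groups". The article gives no strength of association between breastfeeding or time since delivery and either outcome, so those values are assumed below and shown as ranges. It gives no planning figures for VAS, so the arithmetic covers the FSFI only.

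**1. The plan's own figure.** With the normal approximation, n per group = 2 × (1.960 + 0.842)² × 4.5² / 2.4² = 2 × 7.85 × 20.25 / 5.76 = 55.2, rounded up to 56. Allowing for 10% dropout gives 55.2 / 0.9 = 61.3, so 62; or 56 × 1.1 = 61.6, so 62; or 56 / 0.9 = 62.2, so 63. The stated 62 per group reproduces and uses no covariate.

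**2. What the extra covariates could add.** Let R² be the assumed further share of variance explained by breastfeeding status and weeks since delivery at A0. The residual SD is 4.5 × √(1 − R²), the standard error is SD × √(2/56), and power = Φ(2.4 / SE − 1.96).

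| Assumed R² | Residual SD | SE | Power, 56 per arm | n per arm before dropout |
|---|---|---|---|---|
| 0 | 4.500 | 0.850 | 80.6% | 56 |
| 5% | 4.386 | 0.829 | 82.5% | 53 |
| 10% | 4.269 | 0.807 | 84.5% | 50 |

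This treats 4.5 as the SD left after the planned baseline adjustment. If baseline FSFI already brings the SD below 4.5, all three powers are higher and the gaps between them narrower.

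**3. Chance imbalance.** For a yes/no factor with prevalence p, the 95% range of the difference between arms is ±1.96 × √(2p(1 − p)/56). That is ±0.185 at p = 0.5 and ±0.148 at p = 0.8 (prevalences assumed), or about 15 to 19 percentage points. At p = 0.5, an assumed FSFI effect of 2 to 3 points turns this into a shift of up to 0.185 × 2 = 0.37 to 0.185 × 3 = 0.56 points.

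**4. Is that shift additional to the planned uncertainty?** The 95% half-width of the unadjusted difference is 1.96 × 0.850 = 1.67 points. The squared ratio (0.56 / 1.67)² is 0.11. The share of total variance due to a 3-point factor at p = 0.5 is 3² × 0.25 / 4.5² = 2.25 / 20.25 = 0.11. The two agree, so the shift is part of the variability that the standard error already carries.

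**5. Cost in degrees of freedom.** With 112 evaluable women, a model with intercept, arm and baseline outcome leaves 112 − 3 = 109. Two more covariates leave 107.

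**The case against.** The strongest reply is that nothing in section 2.2.6 is invalid. Adjusting for the baseline outcome is standard, randomisation is 1:1, and leaving out a prognostic covariate neither biases the comparison nor inflates the type I error. The section names one adjustment and rules none out, and a fuller covariate list could sit in an analysis plan that is not shown. Baseline FSFI is measured while lactation is already acting, so the planned adjustment absorbs part of the effect. All of this stands, and it limits the point to precision and clarity. It does not remove the mismatch, because the article itself claims that the limitation is addressed and itself states the main adjustment.

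A second reply is that the variables in the Discussion are mostly post-randomisation changes, which should not enter the main model. That is correct. The covariate proposed here is therefore status at A0, with later changes kept for description.

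A third is that the article does not call time since delivery prognostic within the entry window. That also stands. The Discussion says that the source of pain may shift from acute perineal trauma to other structures, and the Introduction mentions new symptoms as activities resume. Both make a link plausible, but neither states one. Weeks since delivery is a reasonable further covariate, with less support in the text than breastfeeding.

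**Conclusion.** The point holds as an inexpensive improvement to a stated analysis. The Discussion offers data collection as the answer to a factor that may influence both primary outcomes, and section 2.2.6 gives those data no use.

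The size is modest. Under an assumed extra R² of 5–10%, FSFI power with 56 evaluable women per arm rises from 80.6% to 82.5–84.5%. The R² is not taken from the article, and no corresponding figure can be given for VAS. The sample size of 62 per group stands.

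A reader might infer more, and the article does not support it:

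- That the estimated radiofrequency effect is biased. It is not, because randomisation protects the comparison. A chance shift of about half a point is the extreme of a 95% range under assumed inputs, lies within the standard error, and is partly absorbed by baseline FSFI.
- That breastfeeding and time since delivery are established drivers of the outcomes. The article says only that lactation-related factors may influence them, and makes no such statement about time since delivery.

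**What to change.** In section 2.2.6, state three things:

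- The baseline-adjusted main comparison of VAS and FSFI also includes breastfeeding status at A0 (yes/no) and, given the width of the entry window, weeks since delivery at A0 (continuous).
- This comparison is a covariate-adjusted model, such as ANCOVA or linear regression. The model has to be named, because the t-test and Mann–Whitney test now listed cannot carry covariates, including the baseline value already promised.
- Post-randomisation changes in breastfeeding and the return of menstruation are described by arm and not adjusted for in the main analysis.

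The Discussion can then refer to this analysis when it says that the limitation is addressed. The cost is a few sentences and two degrees of freedom (109 to 107 with 112 evaluable women). No new data are needed. Fixing the covariates before outcome data by arm are seen also rules out choosing them later.
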